### Statistical analyses

We will describe temporal changes in DAPT prescribing and bleeding for PCI, CABG and ACS populations. We will use descriptive statistics to summarise the characteristics of the different intervention groups and standardised mean differences to compare them. We will estimate rates of bleeding (number of events/person time) with 95% CIs for each group. We will separate major and minor bleeding since adverse events of each type have different health and resource use consequences.

Analyses will estimate the effects of assigned intervention (analogous to an intention-to-treat analysis of a randomised trial) for the antiplatelet regimens corresponding to the first prescription of aspirin or DAPT in CPRD (see Interventions). We will use parametric survival models to estimate adjusted HRs with 95% CIs for the time to first bleeding event, comparing intervention groups for each target trial. Exploratory analyses, including assessment of proportional hazards assumptions, will be used to inform the choice of survival distribution (eg, Weibull). Estimated time-dependent event probabilities will be used to update existing cost-effectiveness models.^26^ The confounding factors to be included in the model (which will be identified as described previously and grouped into confounding domains from our data set), the modelling strategy and the approach to handling correlated covariates will be documented in a data analysis plan. Participants free from a bleeding event will be censored at 12 months after the index event. For secondary endpoints, we will use survival models to estimate adjusted HRs with 95% CIs for time to first event. For mortality outcomes, we will take account of the competing risks of death due to other causes.

We will perform three sets of sensitivity analyses:We will address the unknown intervention group of eligible patients who have no prescription data and therefore cannot be assigned to an intervention (ie, those that died before receiving their first prescription, had a major bleed which caused them to stop DAPT or have no aspirin/DAPT prescription recorded in CPRD within the 2-month window). These analyses will be undertaken using multiple imputation methods to deal with missing information on DAPT medication and will take patient characteristics, procedure/diagnosis and general medication policies into account, using a range of assumptions.We will address the possibility that some minor bleeding events are not documented in CPRD but nevertheless prompt medication changes. We anticipate that most bleeding events will occur soon after the index event and before any medication change. Medication changes will be described relative to bleeding events observed (eg, before event, after event, no bleeding event observed). If a substantial proportion (>10%) of people change medication before their first bleeding event, we will perform a sensitivity analysis excluding these patients.We will assess the sensitivity of our findings when the analysis is restricted to a subpopulation of patients at low risk of bleeding (ie, excluding people at high risk for bleeding) who, we hypothesise, have the lowest risk of residual confounding.

We will attempt to identify an instrumental variable (eg, clinician/GP practice prescribing practice) to control for confounding by indication. If we are successful, we will repeat the above analyses for the PCI, CABG and ACS populations.

We will explore the consistency of treatment effect estimates in the following subgroups: ACS versus non-ACS (PCI and CABG populations); diabetic versus non-diabetic; chronic kidney disease versus non-chronic kidney disease; concurrent prescription for proton pump inhibitors versus no prescription for proton pump inhibitors. All subgroups will be defined in the data analysis plan and chosen based on the characteristics of the analysis populations before carrying out any analyses by intervention group. We will report p values from tests of interaction.

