**Methods and analysis:**

We will use linked Clinical Practice Research Datalink (CPRD) and Hospital Episode Statistics (HES) data to assemble populations eligible for three ‘target trials’ in patient groups: percutaneous coronary intervention (PCI); coronary artery bypass grafting (CABG); conservatively managed (medication only) acute coronary syndrome (ACS). Patients ≥18 years old will be eligible if, in CPRD records, they have: ≥1 year of data before the index event; no prescription for DAPT or anticoagulants in the preceding 3 months; a prescription for aspirin or DAPT within 2 months after discharge from the index event. The primary outcome will be any bleeding event (CPRD or HES) up to 12 months after the index event. We will estimate adjusted HR for time to first bleeding event comparing: aspirin and clopidogrel (reference) versus aspirin and prasugrel or aspirin and ticagrelor after PCI; and aspirin (reference) versus aspirin and clopidogrel after CABG and ACS. We will describe rates of bleeding in patients prescribed TT (DAPT plus an anticoagulant). Potential confounders will be identified systematically using literature review, semistructured interviews with clinicians and a short survey of clinicians. We will conduct sensitivity analyses addressing the robustness of results to the study’s main limitation—that we will not be able to identify the intervention group for patients whose bleeding event occurs before a DAPT prescription in CPRD.

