**Trial registration number:**

76607611; Pre-results.

Strengths and limitations of this studyWe designed our study using the framework recommended by the Cochrane Bias and Non-Randomised Studies Methods Groups for establishing appropriate patient populations, interventions and follow-up to emulate three hypothetical randomised controlled trials (target trials).We will identify potential confounders systematically using literature review, semistructured interviews with clinicians (cardiologists, cardiac surgeons and general practitioners) and a short survey with an additional group of clinicians.Because there are no medication data in Hospital Episode Statistics, we will assume that patients’ first dual antiplatelet therapy (DAPT) prescription that appears in Clinical Practice Research Datalink (CPRD) after their hospital admission is what they were prescribed at discharge.We will conduct sensitivity analyses to address the robustness of results to different assumptions about the unknown intervention group in patients who died or had a bleeding event before a DAPT prescription in CPRD.

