Assignment to interventions	Participants are assigned to DAPT interventions in hospital.	Participants enter the study at index procedure date for PCI and CABG, and episode start date for ACS, and will be assigned to DAPT interventions using first prescription in CPRD (within 2 months of hospitalisation) as a proxy for what they were prescribed in hospital (there are no medications data in HES). This assignment will exclude a proportion of eligible patients (those who died or experienced a major bleed that caused them to stop DAPT, or patients who have no prescription for DAPT within the 2-month window); we will identify and describe the characteristics of these excluded patients. In sensitivity analyses, we will address the robustness of results to different assumptions about the intervention group in those patients where the DAPT medication is unknown or a major bleed occurs prior to the first DAPT medication, by using multiple imputation models for handling missing data. Prior known information regarding the likely prescription based on patient characteristics or general policies will be incorporated in these analyses.
Follow-up	Starts at assignment to intervention and ends at first bleed or 12 months from assignment (whichever comes first).	Starts at time of hospitalisation for PCI, CABG or ACS and ends at first bleed or 12 months from hospitalisation (whichever comes first).
Primary outcome	Any bleed within 12 months of the start of DAPT (DAPT is prescribed at hospitalisation for PCI, CABG or ACS).	Any bleed within 12 months of hospitalisation for PCI, CABG or ACS.
Analysis	Intention to treat	According to first prescription for DAPT in CPRD

CABG, coronary artery bypass grafting; CRPD, Clinical Practice Research Datalink; DAPT, dual antiplatelet therapy; HES, Hospital Episode Statistics; PCI, percutaneous coronary intervention; PICO, Population, intervention, comparator, outcome.

In patients who have undergone PCI, estimate the effect on bleeding events of assignment to aspirin and clopidogrel (reference) versus aspirin and prasugrel or aspirin and ticagrelor.In patients who have undergone CABG, estimate the effect on bleeding events of assignment to aspirin (reference) versus aspirin and clopidogrel.In patients who are conservatively managed after presenting with ACS, estimate the effect on bleeding events of assignment to aspirin (reference) versus aspirin and clopidogrel.

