We will classify patients according to the first prescription recorded in CPRD during the first 2 months after hospitalisation for PCI, CABG or ACS. This 2-month window is based on variability in the amount of DAPT medication provided to patients in hospital following their PCI, CABG or ACS and hence variability in the time when they first request a repeat prescription from their general practice. A preliminary investigation showed that more than 75% of eligible patients have a prescription for one or more antiplatelet agents during this time period. If a patient only has a prescription for aspirin during the 2-month window after hospital discharge, they will be assigned to an aspirin only intervention. If patients also receive a prescription for clopidogrel, prasugrel or ticagrelor, they will be assigned to aspirin/clopidogrel, aspirin/prasugrel or aspirin/ticagrelor. If there is a prescription for more than one additional antiplatelet agent in the 2-month window, we will assign the patient to an intervention based on the agent prescribed first. For example, if a patient has an aspirin prescription and a prescription for clopidogrel before a prescription for ticagrelor, the patient will be assigned to the aspirin/clopidogrel intervention. Patients with no prescriptions in CPRD for aspirin, or aspirin and clopidogrel, prasugrel or ticagrelor within the 2-month window will be excluded from the main analysis. We will conduct sensitivity analyses of all eligible patients including those with unknown DAPT regimens or a major bleed prior to first DAPT prescription, by estimating assignment to DAPT interventions for those with no prescription data using multiple imputation based on a range of assumptions.^20^

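### The plan says in three different ways whose treatment arm is unknown, and sensitivity analysis 1 as written leaves out patients who bleed first and are prescribed afterwards

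*Protocol article*

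**What the plan says.** Follow-up starts at the index procedure, or at the start of the ACS hospital episode (Follow-up). The arm is set by the first CPRD prescription in the next 2 months (Interventions; Table 1, Assignment to interventions). The text states no condition that this prescription must come before the bleed.

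The patients whose arm is regarded as unknown are described as follows:

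- **Abstract, Methods and analysis:** the main limitation is that "we will not be able to identify the intervention group for patients whose bleeding event occurs before a DAPT prescription in CPRD". Any bleed qualifies.
- **Strengths and limitations:** sensitivity analyses will address "the unknown intervention group in patients who died or had a bleeding event before a DAPT prescription in CPRD". Again any bleed, with deaths added.
- **Table 1, Assignment to interventions:** the analyses address "those patients where the DAPT medication is unknown or a major bleed occurs prior to the first DAPT medication, by using multiple imputation models". Major bleeds only, as a category alongside unknown medication.
- **Interventions, last sentence:** the sensitivity population is all eligible patients, "including those with unknown DAPT regimens or a major bleed prior to first DAPT prescription", but the arm is obtained "by estimating assignment to DAPT interventions for those with no prescription data using multiple imputation".
- **Statistical analyses, sensitivity analysis 1:** "We will address the unknown intervention group of eligible patients who have no prescription data and therefore cannot be assigned to an intervention". The explanatory list that follows names death before a first prescription, a major bleed that led to stopping DAPT, and no aspirin or DAPT prescription in the window.

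**The concern.** Take a patient who bleeds on day 10 and has a first GP prescription on day 25. This patient has prescription data, so the wording of sensitivity analysis 1 does not reach them. The arm is read from a prescription written after the outcome and possibly altered because of it. The Abstract presents exactly this situation as the main limitation.

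It matters most for CABG and ACS, where the reference arm is aspirin alone. If a patient started on aspirin and clopidogrel bleeds, stops clopidogrel and is then prescribed only aspirin, the Interventions rule places them in the aspirin arm, and the bleed counts against the reference. Sensitivity analysis 1 lists a major bleed that stopped DAPT among patients without prescription data, but a patient still prescribed aspirin does have prescription data. The text does not settle this case.

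At stake is what the robustness check can show. If early bleeders are handled identically in both analyses, the two can agree while sharing the same misassignment.

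**Working it through.** **Step 1: the definitions side by side.** The question is whether each statement treats the arm as unknown, or imputes it, for three kinds of patient.

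| Place | Minor bleed day 10, prescribed day 25 | Major bleed day 10, prescribed day 25 | No prescription in window |
|---|---|---|---|
| Abstract; Strengths and limitations | Yes | Yes | Only if a bleed (or, in Strengths and limitations, death) came first |
| Table 1 | No | Yes | Yes |
| Interventions, sensitivity population | Not named | Yes | Yes |
| Interventions, imputation clause | No | No | Yes |
| Statistical analyses, sensitivity analysis 1 | No | No | Yes |

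The middle column is contradictory. In the first column, only the general wording of the Abstract and of Strengths and limitations applies; no imputation is specified. Minor bleeds recorded in CPRD are part of the primary outcome (Outcomes: BARC types 2 to 5, from HES and CPRD).

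**Step 2: do the other sensitivity analyses cover the gap?** The second concerns medication changes before the first bleed, which is the opposite order. The third restricts to patients at low bleeding risk. Neither reassigns anyone.

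**Step 3: is the group likely to be empty?** Statistical analyses itself expects most bleeds soon after the index event, while the first prescription may come at any time up to 2 months. The documents do not give the share of bleeds that precede it.

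**Step 4: illustration of size.** The counts and bleeding rates come from Sample size. Expected bleeds:

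- CABG: 595 × 0.09 = 53.6 against 2556 × 0.05 = 127.8
- ACS: 3082 × 0.09 = 277.4 against 8148 × 0.05 = 407.4
- PCI, ticagrelor against clopidogrel: 770 × 0.12 = 92.4 against 6738 × 0.09 = 606.4

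The totals agree with the plan's event counts: 181 for CABG (stated 180), 685 for ACS (680) and 699 for PCI (700).

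Assume a share q of the bleeds in the more intensive arm precedes the first prescription, and a share d of those patients is then recorded on the comparator. With e₁ and n₁ the bleeds and patients in the more intensive arm, and e₀ and n₀ those in the reference arm, the number moved is m = e₁ × q × d, and

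RR = [(e₁ − m)/(n₁ − m)] / [(e₀ + m)/(n₀ + m)]

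| | No movement | q = 0.2, d = 0.1 | q = 0.3, d = 0.2 | q = 0.5, d = 0.3 |
|---|---|---|---|---|
| CABG | 1.80 | 1.75 (m = 1.1) | 1.66 (m = 3.2) | 1.46 (m = 8.0) |
| ACS | 1.80 | 1.75 (m = 5.5) | 1.64 (m = 16.6) | 1.41 (m = 41.6) |
| PCI, ticagrelor | 1.33 | 1.31 (m = 1.8) | 1.25 (m = 5.5) | 1.13 (m = 13.9) |

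For CABG in the last column: (45.5/587.0)/(135.8/2564.0) = 0.0775/0.0530 = 1.46.

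Neither q nor d is in the documents, and movement is assumed to run one way only, from the more intensive arm to the reference. The fall toward 1 follows from that assumption.

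**The case against.** A reader might infer that early bleeders keep their post-bleed regimen in every planned analysis. The documents do not support that. Table 1 extends the imputation to major bleeds before the first DAPT medication, separately from unknown medication, and Interventions names the same group in the sensitivity population. Nothing ranks Statistical analyses above Table 1. This stands, and it limits the point to an inconsistency plus a gap for minor bleeds.

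Figure 1 is said to hold the full inclusion and exclusion criteria and is not available here. It might set bleed-first patients aside, so the statement about the main analysis rests on the classification rule in the text.

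This is also a condensed article that leaves the modelling strategy to a data analysis plan. That would excuse silence about the imputation set, but the article does state the set, and states it inconsistently.

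The illustration uses assumed shares, and at its low end the effect is trivial. Interventions argues that GPs seldom change what the hospital started, and GP interviews are planned to check this, although neither covers a change made in hospital after a bleed. The figures therefore show what is possible and are not an estimate of bias.

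Finally, discarding the observed prescription of every early bleeder has a price. Missingness would then depend on the outcome, and the imputation for these patients would rest on assumption. An extreme case that moves all of them to the more intensive regimen tells little. For ACS, moving 20% to 50% of the 407.4 aspirin-arm bleeds (81 to 204 patients) gives (358.9/3163.5)/(325.9/8066.5) = 2.8 up to (481.1/3285.7)/(203.7/7944.3) = 5.7, against 1.80. This stands and shapes the fix.

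**Conclusion.** The point holds as an inconsistency in scope. The Abstract and Strengths and limitations refer to any bleed before a DAPT prescription, Table 1 to unknown medication or a major bleed, and sensitivity analysis 1 with the imputation clause in Interventions to patients without prescription data. Under the wording of sensitivity analysis 1, patients who bleed and are then prescribed in the window keep the post-bleed regimen there as in the main analysis. Table 1 would rescue the major bleeds; minor bleeds have no specified imputation in any section.

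It would go too far to conclude that the primary hazard ratios are biased by the amounts tabulated. The documents give neither the share of bleeds before the first prescription nor the share of those patients whose regimen changed, nor the direction of change. What follows is that the check on the limitation the authors rank first is not clearly set up to test it. Correcting this changes a sensitivity analysis and leaves the primary estimate as it is.

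**What to change.** Use one definition in the Abstract, Strengths and limitations, Table 1, Interventions and Statistical analyses. In sensitivity analysis 1, treat the arm as uncertain for:

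- (a) patients with no qualifying prescription in the 2-month window; and
- (b) patients with any bleed, major or minor, before the first qualifying CPRD prescription, even if a prescription follows.

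State what counts as a qualifying prescription in each target trial. Impute (b) over a stated range of probabilities that the recorded regimen differs from the one started in hospital, beginning at none changed and moving upward. At zero, group (b) is handled as in the main analysis, so the reader can see how much change it takes to alter the conclusion. Do not use an extreme that assigns all of (b) to the more intensive regimen. Report the number in (b) by observed arm for each target trial.

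The cost is rewording plus one flag from dates already held (first bleed before first qualifying prescription). The downside is a wider interval in this sensitivity analysis and reliance on assumptions for group (b), which should be stated with the result.

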### Triple therapy

We will establish additional groups of patients (PCI or CABG or conservatively managed ACS) based on TT prescription. The main reason for prescribing an anticoagulant is to treat atrial fibrillation in a patient otherwise eligible for either of the three target trials. Atrial fibrillation can precede (long-term anticoagulation for pre-existing atrial fibrillation) or follow the index event (anticoagulation for new-onset atrial fibrillation). Figure 2 shows how the patient groups receiving TT will be constructed.

**Figure 2 F2:**
[figure not shown]
Study diagram describing the construction of the triple therapy (TT) populations.

We will identify patients on long-term anticoagulation by identifying prescriptions of oral anticoagulants (warfarin, dabigatran, rivaroxaban, apixaban) in the 3 months before their index event and a concomitant prescription of any anticoagulant (TT) with DAPT and in the first 2 months after the index admission. Patients who develop atrial fibrillation after the index event will be identified from any new anticoagulant prescription during follow-up. We have compiled a list of all drug codes in CPRD for antiplatelet agents (aspirin, clopidogrel, prasugrel and ticagrelor) and anticoagulants (warfarin, dabigatran, rivaroxaban, apixaban) (see supplementary appendix 3).

10.1136/bmjopen-2019-029388.supp3Supplementary file 3

In patients receiving various TT regimens (grouped by pre-index event anticoagulant prescription and post-index event anticoagulant prescription in PCI, CABG and ACS separately, see figure 2), we will describe rates of bleeding (number of events/person time) with 95% CIs for each group. We have not specified comparison groups because we know there is large variation in prescribing of anticoagulants; TT is usually prescribed for a relatively short period of time (1–6 months, depending on a patient’s individual risks of thrombosis and bleeding) after which an antiplatelet agent (usually aspirin) is removed and patients continue to receive an anticoagulant and single antiplatelet for the remainder of the 12 months after the index admission.

### Patient and public involvement

We set up a patient advisory group comprising of patients from our three cohorts (PCI, CABG and conservatively managed ACS). The group was consulted about several aspects of the proposed study. Group members confirmed the importance of the research topic and agreed that the choice of antiplatelet regimen should be based on shared decision making, with clinicians and patients weighing the potential benefits against the adverse side effects and practical inconvenience. Our PPI group will attend regular meetings to discuss results from the study and will also contribute and collaborate on the development of our results dissemination strategy.

### Ethics and dissemination

This study protocol has approval. We also obtained ethical approval for the semistructured interviews with clinicians and survey from South West Cornwall and Plymouth Research Ethics Committee, 17/SW/0092. The findings will be presented at national/international conferences, published in peer-reviewed academic journals and accessible formats in newsletters to patients (where available). The findings will also be reported as a briefing paper to commissioners (eg, commissioning groups, National Institute for Health and Care Excellence) and to other healthcare stakeholders with an interest in the research through the Cardiac & Stroke Networks. We will also present and discuss our results at local CPRD working groups to disseminate methods to other researchers using the CPRD database.
